## Abstract

The swallowing function is often compromised immediately after general anesthesia owing to the effects of anesthetic agents. Consequently, pharyngeal residue may accumulate, which increases the risk of aspiration during the perioperative period. Therefore, we designed a single-arm, open-label study, developing an artificial intelligence (AI)-based acoustic analyzer for quantifying pharyngeal residues and evaluating its efficacy. A sample of 30 patients aged ≥18 years scheduled for jaw deformity surgery will be enrolled in this study. Immediately after tracheal tube extubation, adventitious sounds from pharyngeal residues, such as saliva and blood, will be measured and quantified using an AI acoustic analysis system. Subsequently, the residual pharyngeal fluid will be suctioned and quantified by measuring the change in container weight before and after collection. The primary outcome measure will be the comparison of adventitious sounds before and after pharyngeal suction, and the secondary outcome will be the correlation between pharyngeal residue volume and adventitious sounds. The results of this study are expected to be drawn by 2025 upon its completion. This study will demonstrate the feasibility of AI-based acoustic monitoring for quantifying increased pharyngeal residues during perioperative management. This approach has the potential to reduce the risk of postoperative aspiration with a simple and inexpensive method.

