**Figure 1 FIG1:**
[figure not shown]
Schema of the study protocol.

Table 2 shows the SPIRIT schedule for patient enrollment, interventions, and assessments.

**Table 2 TAB2:** SPIRIT schedule of enrollment, interventions, and assessments. Table 2 shows the SPIRIT schedule for patient enrollment, interventions, and assessments.

Study period	Pre-Enrolment	Enrolment	Post-Enrolment	Close-out
Time point	-1 day	0 day	+1 day	
Enrolment	X			
Eligibility screen	X			
Informed consent	X			
Respiratory sound monitoring		X		X
Collection of pharyngeal residual fluid		X		X
Residual fluid in the pharynx		X		X
Respiratory sound analysis		X		X

Procedure

Propofol, remifentanil or fentanyl, and rocuronium will be used for general anesthesia. Intraoperative monitoring includes electrocardiography, oxygen saturation measurements, capnography, bladder temperature measurements, electroencephalography, and neuromuscular function measurements. Extubation during emergence will be performed once the train-of-four (TOF) ratio and the Entropy index (GE Healthcare’s Brain Monitoring System) have recovered to at least 90% and it is confirmed that the patient can open their eyes, open their mouth, and elevate their tongue.

The study procedure is illustrated in Figure 1. Immediately after extubation, the respiratory sound monitoring device will be attached to the skin of the neck (paralaryngeal region) and chest (beneath the sternal notch) using an adhesive tape (TransporeTM, White, 3M, USA). Subsequently, respiratory sound sampling will be initiated. After three minutes of sampling, the residual pharyngeal fluid will be suctioned using a McGrathTM MAC videolaryngoscope (Aircraft Medical Ltd., Edinburgh, UK), and an additional three minutes of respiratory sound recording will be performed. The residual pharyngeal fluid will be aspirated into a container (Triple Seal CapTM, AGC Techno Glass Co., Shizuoka, Japan; Figure 2), and after suctioning, the residual material inside the suction tube will also be flushed using 20 mL of normal saline. The weight of the pharyngeal residual substance will be measured as the change in the weight of the container before and after fluid collection.

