**Figure 2 FIG2:**
[figure not shown]
Containers for collecting residual pharyngeal fluid. Red arrow: Connect this end to the suction device.

Data collection

Two anesthetists will confirm the clinical evaluation and anesthetic records, and the following data will be recorded: height, weight, sex, degree of obesity, presence of respiratory disease, presence and degree of sleep apnea, Cormack-Lehane grading, presence of dysphagia, history of head and neck surgery, and presence of serious allergies. Six anesthesiologists will collect the auscultation data, and the presence or absence of profuse nasal bleeding and compliance with monitoring procedures will be recorded. 

The auscultation data will be stored as comma-separated value (CSV) files generated at one-second intervals from AI-based analyses, and these data will be cross-referenced with the corresponding WAV audio files. Within the three-minute recording periods before and after pharyngeal suctioning, auscultation segments with minimal noise and patient movement will be identified. Among these segments, we will determine the segments intended as reference intervals for the comparison of adventitious sound indices. If sensor detachment, application freezing, or noncompliance with sampling procedures for pharyngeal residue is observed during data acquisition, data collection is discontinued.

Statistical analysis

The 30-second mean values of the adventitious sound index measured before and after suction will be calculated, and a paired t-test will be performed for each of the three categories of the index. To determine the superior monitoring location, the index values obtained before suction will be subjected to analysis of variance for each type of index at both the cervical and thoracic monitoring sites. Statistical significance will be set to p < 0.05. significant. All statistical analyses will be conducted using SPSS v. 25 for Mac (IBM Corp., Armonk, NY).

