The acoustic sensor employed in the process is a cost-effective displacement-detection vibration sensor. By clarifying the sensor installation requirements necessary for identifying pharyngeal residues through acoustic monitoring, a novel evaluation method for quantifying the perioperative aspiration risk may be established, it is envisaged that the device will establish a widely applicable pharyngeal residue assessment index. Nevertheless, several limitations are identified in the method used to validate this research. First, the collected liquid residue contains various substances, including blood, saliva, and mucus. Although changes in weight serve only as a quantitative indicator, it remains unclear which types of fluid pose the aspiration risk. Furthermore, the findings may not be generalizable to surgeries other than those involving the head and neck. Second, the evaluation of pharyngeal residue using the adventitious sounds index is subject to confounding factors, including obesity, upper airway obstruction such as sleep apnea, and underlying conditions like tonsillar hypertrophy. In particular, a correlation has been reported between obesity, body mass index (BMI), and the adventitious sounds index [7]. These confounding factors will be documented, and a multivariate analysis will be performed. Third, the inability to restrict the patient’s swallowing has been identified as a concern. When the pharyngeal residue is swallowed by the patient, the amount of residue is inevitably reduced. Fourth, it should be noted that the adventitious sounds index can be increased by environmental noise, as well as by the patient’s own vocalization or coughing.

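### The primary before/after t-test counts any spontaneous change after extubation as the effect of suction, and the stored pre-suction recording could supply a supportive check

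*Protocol article*

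**What the plan says.** The Abstract describes the design ("we designed a single-arm, open-label study") and the primary outcome: "The primary outcome measure will be the comparison of adventitious sounds before and after pharyngeal suction".

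The Procedure section fixes one sequence for all patients. "Immediately after extubation, the respiratory sound monitoring device will be attached to the skin of the neck (paralaryngeal region) and chest", and sound sampling begins. Then: "After three minutes of sampling, the residual pharyngeal fluid will be suctioned" under videolaryngoscopy, and "an additional three minutes of respiratory sound recording will be performed".

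The Data collection section says that index values are stored every second and checked against the audio. Comparison segments are chosen in each three-minute period for low noise and little movement. The article gives no rule for where in the period they lie.

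In the Statistical analysis section, "The 30-second mean values of the adventitious sound index measured before and after suction will be calculated". These means are then compared by paired t-tests, one per category of the index. No time term or comparison within the pre-suction period is described.

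The limitations in the Discussion say that swallowing cannot be prevented: "When the pharyngeal residue is swallowed by the patient, the amount of residue is inevitably reduced". They add that noise, talking and coughing can raise the index. A multivariate analysis is announced for obesity, upper airway obstruction such as sleep apnea, and conditions such as tonsillar hypertrophy.

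**The concern.** Suction always comes second, so its effect is completely confounded with time since extubation. The Introduction attributes poor swallowing at this stage to residual anesthetics, narcotics and pain, which gives reason to expect some change over these minutes even if nothing is done. The paired test estimates the sum of the suction effect and that spontaneous change.

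The stated safeguards act elsewhere. Segment selection removes noisy or restless stretches but leaves a trend across the quiet ones. The multivariate analysis uses patient characteristics, so the mean within-patient change still contains the drift. The chest sensor addresses where a sound arises, not how it changes with time.

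At stake is the wording of the primary conclusion. A downward drift could be read as a suction effect, and an upward one could hide a true fall. Yet each patient contributes three minutes without suction, from which the trend could be estimated.

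**Working it through.** **Inputs (Sample size calculation section).** Means 0.0679 and 0.1415, so the planned difference is 0.1415 − 0.0679 = 0.0736. Effect size 0.58, two-sided 5%, 80% power, 26 evaluable, about 10% dropout, 30 enrolled.

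**1. Reproducing the plan's figure.** An exact paired t-test (noncentral t, df = n − 1) with standardised difference 0.58 needs n = 26, with power 81.1%. For dropout, 26/0.9 = 28.9, so 29 against the stated 30. The sample size is not in question. At n = 30 the power is 86.7%.

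**2. Implied SD of the differences.** 0.0736/0.58 = 0.127. This comes from patients with obesity given oral water, not from recordings after extubation.

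**3. What becomes significant at n = 30.** The smallest significant standardised mean change is t(0.975, 29)/√30 = 0.373. In index units, 0.373 × 0.127 = 0.047, or 64% of the planned effect, whatever its cause.

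**4. Drift with no suction effect.** The drift sizes are assumptions. With drift equal to a fraction f of the planned effect, the noncentrality is f × 0.58 × √n.

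| f | Drift (index units) | P(significant), n = 26 | P(significant), n = 30 |
|---|---|---|---|
| 0 | 0 | 5% | 5% |
| 0.25 | 0.018 | 11.0% | 12.0% |
| 0.50 | 0.037 | 29.6% | 33.6% |
| 0.75 | 0.055 | 56.8% | 63.4% |
| 1.00 | 0.074 | 81.1% | 86.7% |

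**5. Using the pre-suction recording.** Let E and L be early and late pre-suction window means and P the post-suction mean. With equal spacing the contrast is D = (L − P) − (E − L). Linear drift cancels. In a simulation (40,000 runs, n = 30, no suction effect, linear drift, equal spacing), the simple test was significant in 5.0, 11.9, 33.2 and 86.6% of trials at f = 0, 0.25, 0.5 and 1. D stayed at 5.0% throughout.

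**6. Cost in precision.** With equal window variance s² and common correlation ρ, var(L − P) = 2s²(1 − ρ). Since D = 2L − E − P, var(D) = 6s²(1 − ρ), so the SD grows by √3. The table gives the effect size and power for a true suction effect of 0.58.

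| Assumption on the no-suction change | Effect size for D | Power, n = 30 | Evaluable n for 80% |
|---|---|---|---|
| Same SD, single equal-noise windows | 0.58/√3 = 0.335 | 42.6% | 72 |
| Same SD, independent | 0.58/√2 = 0.410 | 58.4% | 49 |
| Half the SD, correlation −0.5 | 0.58/√1.75 = 0.438 | 64.1% | 43 |
| Half the SD, independent | 0.58/√1.25 = 0.519 | 78.4% | 32 |

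**7. Why window position matters.** Let S be the suction time in seconds, which is not stated. Pre-suction window centres can lie from 15 to 165 s and post-suction centres from 195 + S to 345 + S. The separation can therefore be anything from 30 + S to 330 + S. Over the longer gap, more drift enters the primary difference.

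**The case against.** The case on the other side has real force.

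- **Coughing and talking.** A reader might infer that the analysis ignores them. It does not: selecting quiet segments and checking them against the audio bears directly on both. What remains is drift within the quiet segments.
- **Recovery.** Extubation waits for recovery of neuromuscular function and the Entropy index and for response to commands. That limits later drift but does not exclude it.
- **Swallowing.** A reader might infer that swallowing biases the study against its own question. The Study design section states the aim as the association between residue and index. A fall caused by swallowing is still a fall in residue, so it supports that association and weakens only the attribution to suction. Swallowing before the pre-suction window shrinks the contrast, which is conservative.
- **Other evidence.** The secondary correlation with weighed residue mass is separate evidence, and a drift common to all patients would not by itself create it. A reader might infer that a significant primary result would say nothing about residue. The documents do not support that.
- **Disclosure.** The single-arm design and the limitations are stated openly, and exact window timing may be set in a fuller document that is not shown.

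These points narrow the concern. They do not change what the primary test estimates: the suction effect plus spontaneous change.

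**Conclusion.** The point holds as a limit on interpretation and as a cheap improvement. The stated primary test cannot separate suction from spontaneous change, and none of the stated analyses removes within-patient drift.

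The 12, 34 and 63% figures rest on three assumptions: a drift size, a paired SD of 0.127 carried over from the earlier water study, and 30 evaluable patients. They show what drift would do if present. They do not show that drift is present, and the documents give neither its size nor its direction.

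It would also go too far to infer that the pre-suction contrast settles causality. It is exact only if the earlier trend continues linearly on the same time scale. The pre-suction period contains no laryngoscopy, so the contrast cannot distinguish residue removal from a response to that procedure.

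**What to change.** 1. Fix the window positions in advance by a rule, for example the clean 30 seconds nearest to a set time in each recording. Windows close to suction admit less drift, but a post-suction window there is nearest to any response to laryngoscopy. The rule need not force the first one.
2. From the stored one-second data, report with confidence intervals (a) the early-to-late change within the pre-suction recording, E − L, and (b) the across-suction change minus this no-suction change.
3. Put both on the same time scale. With centres at 15 s and 165 s before suction (150 s apart), equal spacing puts the post-suction centre 135 − S seconds into the second recording. That is possible while S is at most 120 s. Otherwise use (L − P) − (g/h)(E − L), where g and h are the elapsed times across suction and within the pre-suction recording.
4. Present this as a supportive analysis judged by estimate and interval, not as a significance gate on the primary result. If the pre-suction period shows a comparable fall, limit the conclusion to a before/after change.
5. State as limitations that the contrast assumes the pre-suction trend continues and cannot separate residue removal from a response to laryngoscopy.

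Cost: no new patients, procedures or recordings. Each patient needs one more clean 30-second window. The interval is wider than for the simple difference (power about 43 to 78% at n = 30 against 86.7%), which is why the analysis should not decide the trial.

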## Materials and methods

Ethical considerations

This study was approved by the Hiroshima University Certified Review Board (approval number: E2024-0025) and registered at UMIN (UMIN000055020). Written informed consent will be obtained from all patients or their guardians.

Study design

The first draft of the study protocol was finalized on April 18, 2024, following the Standard Protocol Items: Recommendations for Interventional Trials (SPIRIT) Reporting Guidelines. Table 1 presents the primary and secondary objectives of this study. The primary endpoint of this study is to identify the association between pharyngeal residue levels and the adventitious sound index. In addition, we aim to clarify the feasibility of monitoring aspiration risk using the newly developed AI-based adventitious sound analysis system. The secondary endpoints are to verify the correlation between the pharyngeal residue volume and adventitious sounds. 

**Table 1 TAB1:** Primary and secondary endpoint.

Endpoints	Details
Primary	Acoustic sensors will placed on the neck and chest to compare the adventitious sound index before and after aspiration of pharyngeal residues at each location.
Secondary	(1) Correlation between the mass of pharyngeal residue and the adventitious sound index. (2) Acoustic sensors will be placed on the neck and chest to compare the adventitious sound index before aspiration of pharyngeal residues at each location.

Sample size calculation 

A single-arm, pre-post comparison study was previously conducted among 19 patients with obesity who underwent anesthesia monitoring using an acoustic monitoring device. The adventitious sound index was measured before and after intraoral water injection during monitored anesthesia. The mean ± standard deviation of the indeterminate sound INDEX before and after water injection was 0.0679 ± 0.056 and 0.1415 ± 0.111, respectively. Based on these measurements, an effect size of 0.58 was calculated using G*Power software (version 3.1.9.6, Heinrich-Heine-Universität Düsseldorf, Düsseldorf, Germany). Using a two-sided test at a 5% significance level, 26 participants are required to maintain 80% statistical power. After accounting for an anticipated dropout rate of approximately 10%, a final sample of 30 participants is deemed necessary.

Inclusion and exclusion criteria

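### The primary comparison consists of three co-equal paired t-tests (six if run at both sites) at p < 0.05, with no lead test or success rule, while the sample size covers one test only

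*Protocol article*

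**What the plan says.** Table 1 gives the primary endpoint as sensors on neck and chest used "to compare the adventitious sound index before and after aspiration of pharyngeal residues at each location". The Statistical analysis section takes 30-second means before and after suction and states that "a paired t-test will be performed for each of the three categories of the index". It adds one threshold for all analyses: "Statistical significance will be set to p < 0.05".

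The Sample size calculation uses one pair of means and standard deviations for one index from an earlier study of 19 patients with obesity. It reports that "an effect size of 0.58 was calculated using G*Power software" and concludes: "Using a two-sided test at a 5% significance level, 26 participants are required to maintain 80% statistical power". Allowing for about 10% dropout, it arrives at 30.

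The article does not say which of the three categories the 0.58 belongs to. It does not say which category or site leads the primary analysis, or whether one significant result is enough.

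**The concern.** The sample size describes a study with one primary p-value, and the analysis section describes one with several. What the stated 5% and 80% refer to then depends on a rule that the article does not give.

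- If one significant category at one site is enough, the primary claim has several chances to succeed by luck.
- If every test must be significant, the chance of missing a real effect is larger than planned.

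The Conclusions already say that the study will demonstrate feasibility. Without a named lead test, a single positive category at one site could be presented as that demonstration.

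**Working it through.** **Inputs.** Effect size d = 0.58, two-sided alpha 0.05, power 80%, 26 evaluable, about 10% dropout and 30 enrolled (Sample size calculation); three categories and p < 0.05 (Statistical analysis); two sites (Table 1). Evaluable number at 10% loss: 30 × 0.9 = 27. The documents give no correlation between the tests, so I assume 0 to 0.9, equal for all pairs.

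**Step 1: reproduce the plan's figure.** Power of a paired t-test comes from the noncentral t distribution with n − 1 degrees of freedom and noncentrality d√n.
- n = 25: 79.5%. n = 26: 81.1%. So 26 is the smallest n that reaches 80%, as stated.
- 26 / 0.9 = 28.9, so 29 enrolled; the plan rounds up to 30.
- At n = 27, power is 82.7%.

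The stated number is therefore a one-test calculation.

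**Step 2: count the tests.** The t-test sentence gives three, one per category. Joined to Table 1, which asks for the comparison at each of two sites, it gives 3 × 2 = 6.

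**Step 3: any significant test counts as success.** For k independent tests, the chance of at least one false positive is 1 − 0.95^k.
- k = 3: 1 − 0.95³ = 14.3%.
- k = 6: 1 − 0.95⁶ = 26.5%.

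For correlated tests I simulated the paired t-tests at n = 27 (100,000 runs per setting):

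| Correlation | 3 tests | 6 tests |
|---|---|---|
| 0.3 | 13.6% | 24.2% |
| 0.5 | 12.6% | 21.0% |
| 0.7 | 11.0% | 17.0% |
| 0.9 | 8.5% | 11.0% |

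**Step 4: all tests must succeed.** The overall error is at most 5%. Power at n = 27, with an effect of 0.58 in every test:
- Independent: 0.827³ ≈ 57% for three tests; 0.827⁶ ≈ 32% for six.
- Correlation 0.5 (simulated): 65% and 52%.
- Correlation 0.9 (simulated): 75% and 71%.

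**Step 5: Bonferroni correction.**
- Power of any one given test at n = 27: 67.5% at 0.05/3 and 56.9% at 0.05/6.
- Restoring 80% for a given test needs 35 evaluable (35 / 0.9 = 38.9, so 39 enrolled) for three tests, or 40 evaluable (40 / 0.9 = 44.4, so 45 enrolled) for six.
- Power to win on at least one test, with equal effects (simulated, n = 27), is 97% for three and 99% for six at correlation 0. It is 84% for both at 0.7, about 81% and 80% at 0.8, and 77% and 73% at 0.9.

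**The case against.** The other side has four fair arguments.

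**The count of six is inferred.** This stands. The t-test sentence names no site; the sites appear in Table 1 and in the next sentence, on the analysis of variance. The wording of the analysis alone fixes three tests, so both counts are shown.

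**Error inflation depends on an unwritten rule.** This also stands. A reader might infer that the false-positive risk of the primary claim is simply several times 5%. The documents do not support that as a fact: it requires that any one significant test counts. These are also categories of one index in the same patients, so high correlation is plausible. At 0.9 the figure is 8.5% for three tests and 11% for six.

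**Correction need not destroy power.** A reader might infer that any later adjustment forfeits the 80%. That mixes two success rules. The 67% and 57% are powers for one given test. The power to win on at least one corrected test is 84-99% at correlations from 0 to 0.7 if effects are equal, and falls below 80% only when correlation is very high. With unequal effects it could be lower.

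**Multiplicity may be left to an analysis plan that is not shown.** This stands in part. Silence on adjustment would be weak evidence in a condensed article. But the article itself states several co-equal tests, their threshold and a sample size for one of them, and that mismatch is on the page. The article does not claim a family-wise 5%, and each single test does have its 5% and about 81% power at n = 26.

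**Conclusion.** The point holds in a limited form and should be fixed. The plan sets three co-equal primary tests, or six if Table 1 is applied to each site, against a sample size for one. The stated error rate and power are right for each test taken alone. For the overall primary claim, neither success rule delivers both: an any-test rule gives about 8-14% (three) or 11-27% (six) false-positive risk, and an all-tests rule gives about 57-75% or 32-71% power at n = 27.

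These ranges rest on assumed equal correlations of 0 to 0.9 between tests and, for power, on an effect of 0.58 in every test. The documents give neither. The reproduced sample size and the mismatch itself need no such assumption.

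**What to change.** Before any data are seen, name one index category at one site as the single primary test: before minus after suction, two-sided 0.05. The natural choice is the category behind the 0.58, which the article should identify, at the neck, where the Discussion says the earlier studies placed their sensors. Make the remaining category-by-site tests secondary with Holm adjustment, or label them exploratory.

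This takes one sentence in Table 1 and one in the Statistical analysis section, and 30 patients remain enough on the plan's own assumptions. The price is that the other categories and the chest site can no longer carry the primary claim. If the investigators want all of them to carry it, they should state the success rule and re-size. For example, Bonferroni with 80% power per test needs 39 enrolled for three tests or 45 for six.

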## Discussion

In our previous single-cohort intervention study, we demonstrated that the adventitious sound index responded significantly when water was instilled into the oral cavities of patients managed under monitored anesthesia care. However, this previous study did not confirm whether the instilled water actually accumulated in the pharynx [6]. Therefore, using the present protocol, we plan to clarify the correlation between the adventitious sound index and pharyngeal residue by collecting and weighing the pharyngeal residue immediately after awakening from general anesthesia using a video laryngoscope. We will also compare the adventitious sound index before and after this procedure. Using this approach, we expect to elucidate the correlation between pharyngeal residues and adventitious sound indices.

In our previous studies, the sensors for respiratory sound monitoring devices were positioned in the peripharyngeal region [6,7], and increases in the adventitious sound index observed at this site were presumed to result from airflow alterations synchronized with inspiration driven by the pharyngeal residue. However, adventitious sounds have also been identified as arising from bubbling sounds related to intratracheal secretions [8]. Consequently, we could not exclude that the increased adventitious sound index detected in the neck region may have been produced by intratracheal secretions rather than pharyngeal residues. In the current study, we plan to place sensors on both the neck and chest. By comparing the adventitious sound indices at these two anatomical sites, we anticipate that the origin of adventitious sounds could be precisely identified.

Our study group reported that the respiratory sound monitoring system used in this study can quantify the level of adventitious sounds generated in the pharyngeal region by the infusion of water into the oral cavity [9-11]. Furthermore, it has been reported that the adventitious sounds index utilized by this AI system demonstrates approximately 80% sensitivity and specificity relative to physicians’ auscultatory assessments [4]. The adventitious sounds index is calculated at a rate of one frame per 12 milliseconds, enabling real-time and multi-channel monitoring of these sounds. It is anticipated that this system could be widely utilized for aspiration risk monitoring in various clinical situations. 

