In another study, pharyngeal residue was evaluated by attaching an acoustic sensor to the neck (paralaryngeal region) to measure adventitious sounds [12,13]. Although paralaryngeal auscultation with a traditional analog stethoscope is commonly employed in clinical practice to detect pharyngeal residue, it is necessary to exclude or consider the possible influence of adventitious sounds from the lungs when performing automatic respiratory sound analysis [14,15]. Therefore, in the present study, auscultation of the chest (at the upper sternal border) will also be conducted, and the magnitudes of the adventitious sound indices obtained from both sites will be compared. Lung diseases are added to the exclusion criteria, and the influence of adventitious sounds transmitted from the lungs is eliminated by performing endotracheal suctioning before extubation. By doing so, we can specifically infer the adventitious sounds arising solely from pharyngeal residue.

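### The monitoring site is to be chosen from pre-suction index levels, which do not show whether a site responds to removal of pharyngeal residue

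*Protocol article*

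**What the plan says.** The Statistical analysis section gives the rule for choosing a site: "To determine the superior monitoring location, the index values obtained before suction will be subjected to analysis of variance", done for each type of index at the neck and chest. Secondary endpoint (2) in Table 1 matches it: sensors at both places are used "to compare the adventitious sound index before aspiration of pharyngeal residues at each location".

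The response to suction is analysed elsewhere. The primary endpoint in Table 1 is to "compare the adventitious sound index before and after aspiration of pharyngeal residues at each location", and the Statistical analysis section adds that "a paired t-test will be performed for each of the three categories of the index". Secondary endpoint (1) is the correlation between residue mass and the index. Neither result is tied to the choice of site.

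On the source of the sounds, the Discussion says: "By comparing the adventitious sound indices at these two anatomical sites, we anticipate that the origin of adventitious sounds could be precisely identified". It later says that "the magnitudes of the adventitious sound indices obtained from both sites will be compared". It also relies on excluding lung disease and states that "the influence of adventitious sounds transmitted from the lungs is eliminated by performing endotracheal suctioning before extubation".

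**The concern.** The index is meant to signal pharyngeal residue, so the better site is the one whose index follows residue. A level taken before suction adds up every source at that site. The Discussion itself concedes that the neck signal in earlier work may have come from intratracheal secretions, and it lists vocalisation and coughing among things that raise the index. Two sites can therefore differ in level for reasons unrelated to residue.

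The design contains the step that separates these sources: pharyngeal fluid is suctioned between two three-minute recordings. The fall in the index across that step, compared between sites, bears directly on which site responds to residue. The stated rule does not use it.

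At stake is the sensor-placement recommendation, which the Discussion presents as a route to a new measure of aspiration risk. Followed as written, the rule could recommend a site that does not respond, or find no difference between a site that responds and one that does not.

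**Working it through.** **Planning figure.** The plan gives an effect size of 0.58, two-sided 5% significance and 80% power, and arrives at 26 patients. A paired t-test with the noncentral t distribution gives power 0.811 at n = 26 and 0.795 at n = 25, so 26 reproduces. That calculation concerns a before/after comparison. No sample size or power is stated for the comparison between sites.

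**Inputs from the Sample size calculation section.** Index 0.0679 ± 0.056 without instilled water and 0.1415 ± 0.111 with it; difference 0.1415 − 0.0679 = 0.0736.

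**Assumptions not in the documents.**
- Neck: falls from 0.1415 (SD 0.111) to 0.0679 (SD 0.056), before and after uncorrelated.
- Chest: does not respond; SD 0.111 at both times, before/after correlation 0.5.
- Correlation ρ between the pre-suction values at the two sites: 0 to 0.5.
- n = 26, two-sided 5% tests.

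**Step 1: what the pre-suction comparison detects.** For a chest mean that lies Δ above the neck mean, a within-patient test has

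SD of difference = 0.111 × √(2(1 − ρ)) = 0.157 at ρ = 0, or 0.111 at ρ = 0.5

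noncentrality = √26 × Δ / SD of difference

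For Δ = 0.0736 this is 5.099 × 0.0736 / 0.157 = 2.39 at ρ = 0, and 5.099 × 0.0736 / 0.111 = 3.38 at ρ = 0.5.

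| Chest minus neck before suction | Chest declared higher, ρ = 0 | ρ = 0.5 |
|---|---|---|
| 0 | 2.5% | 2.5% |
| 0.0368 | 21% | 37% |
| 0.0736 | 63% | 90% |
| 0.111 | 93% | 99.8% |

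The after-suction values appear nowhere in this formula, so the result is the same whether or not either site responds. In the first row the neck is also favoured in 2.5% of trials, the error rate, although only the neck responds.

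**Step 2: what the within-site tests show.** The SD of the neck change is √(0.111² + 0.056²) = 0.124, so the standardised change is 0.0736 / 0.124 = 0.59 and the power is about 83%. The chest is significant in about 5% of trials. The plan would therefore usually show a response at the neck. It has no test of whether the two responses differ, and no rule that uses them to choose the site.

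**Step 3: the between-site contrast in change.** Take (before − after) at the neck minus (before − after) at the chest in each patient. The chest change has variance 2 × 0.111² × (1 − 0.5) = 0.111². The covariance of the two changes is taken as ρ × 0.111² × (1 − 0.5).

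Variance of contrast = 0.111² + 0.056² + 0.111² − 2 × 0.5 × ρ × 0.111²

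- ρ = 0: SD 0.167; noncentrality 5.099 × 0.0736 / 0.167 = 2.25; power about 58%.
- ρ = 0.5: SD 0.147; noncentrality 5.099 × 0.0736 / 0.147 = 2.55; power about 69%.

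The chest level does not enter. The contrast responds to what suction removes and ignores a constant background at either site. Simulation of 20,000 trials per scenario agrees with steps 1 to 3 to within about one percentage point.

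**The case against.** The strongest reply is that the response to suction is already the primary endpoint at each location. A site that does not respond would be visible there, beside the site comparison, and secondary endpoint (1) adds the correlation with mass. This stands in part: the information is collected and analysed. But the stated rule for the site does not refer to it, and one significant and one non-significant before/after test do not establish that the sites differ.

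Four stronger readings are tempting, and the documents do not support them.

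- *The origin of the sounds is decided from pre-suction levels alone.* The Discussion does not restrict its two-site comparison to pre-suction values, and it adds lung-disease exclusion and endotracheal suctioning as grounds. The most that can be said is that the origin inference appears to rest partly on the same level comparison.
- *The site comparison ignores pairing.* The text says only analysis of variance. A repeated-measures form is one, and the exact model may be in a fuller document. A clarification is worth asking for; an error is not shown.
- *The noisier site wins.* Segments with little noise and movement are to be selected, so the accurate description is the site with the higher index. That selection does not remove tracheal sound or differences in baseline between sites. That the higher index is the winner is the natural reading of the rule but is not stated.
- *The percentages measure the defect.* They depend on an assumed chest level, spread and correlation.

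**Conclusion.** The concern holds for the location decision. The rule in the Statistical analysis section, matched by secondary endpoint (2), rests on a quantity that cannot distinguish a site that responds to residue from one that does not. The gap is the missing link between the suction response and the choice of site, not missing data.

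Under the assumptions above, an unresponsive chest with a mean 0.0736 above the neck's is declared higher in about 63% to 90% of trials. With equal levels, the test favours either site only at the error rate. The size in this trial is unknown because no chest data are given, but the logic does not depend on the figures.

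This should be fixed. It affects a secondary endpoint and leaves the primary analysis and the sample size untouched.

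**What to change.** For each index, base the location decision on the within-patient contrast: (before minus after) at the neck minus (before minus after) at the chest, tested with a paired t-test. This is equivalent to the site-by-time interaction in a repeated-measures analysis of variance. Report the estimate with a confidence interval, because under the illustration its power at 26 patients is only about 58% to 69%. Report each site's correlation with residue mass alongside; it does not depend on the two sites sharing a scale.

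Keep the pre-suction comparison as descriptive, analysed within patient because both sites are recorded in the same patients. Amend secondary endpoint (2) and the Discussion's wording on origin to match.

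The cost is analysis wording only. All four recordings per patient (two sites, before and after) are already planned.
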